**Figure 2 figure2:**
[figure not shown]
Freezing-inducing path (adapted from Pardoel et al [32], which is published under Creative Commons Attribution 4.0 International License [33]).

Participants will undergo testing under different dual-task conditions, which are recognized for promoting FoG episodes [32]. The DMT involves walking with a ball on a tray within a drawn circle, keeping the ball centered. The DCT requires participants to generate as many words as possible starting with a specified letter. Each participant will complete a maximum of 6 blocks, with each block consisting of the 3 conditions (ST, DCT, and DMT), resulting in a total of 18 trials (6 blocks × 3 conditions per block). The sequence of conditions within each block will be randomized to mitigate any order effects. This protocol accommodates varying endurance levels among patients; some may complete each block quickly with few or no FoG episodes, while others may take longer due to frequent tremors that consume energy. This flexible approach ensures that the study is comprehensive and respects each patient’s physical limitations. However, participants who complete fewer than 2 blocks (6 trials) will be excluded from the analysis to ensure adequate data collection.

### Data Collection (and Preprocessing)

#### Clinical Data

Various patient data are collected, including age, sex, laterality of symptoms, duration of PD, lateralization of symptom onset, daily dose of levodopa equivalent, MDS-UPDRS III score [27], Freezing of Gait Questionnaire (FoGQ; “on” and “off” phases) [34], Hoehn and Yahr Scale (“on” and “off” phases) [35], and Schwab and England Scale (“on” and “off” phases) [36]. The FoGQ is used to assess the characteristics of FoG. The Hoehn and Yahr Scale and the Schwab and England Scale serve as tools for the overall evaluation of patients with PD: the former to gauge disease severity and the latter to evaluate daily life impact, functional status, and level of dependence.

#### FoG Measurement

##### IMU Measurements

Patients will wear the Trigno Avanci IMU (Delsys; Figure 3), which includes a triaxial accelerometer, gyroscope, and magnetometer. Data will be transmitted via Bluetooth and collected using the Delsys application programing interface and then transferred to QTM 2020 software (Qualisys). The software manages recording at a sampling frequency of 148.15 Hz and synchronizes with cameras. While this sampling frequency is higher than that in some studies, it has been previously used, similar to the approach taken by Camps et al [37]. This frequency is selected to ensure that all nuances associated with FoG, particularly micromovements, are captured. IMU data will also undergo windowing with a 2-second window length and a 0.4-second shift. A trained operator will position the sensors manually, aligning them with anatomical axes. Seven IMUs will be placed as follows: 1 on each thigh (lateral side, upper third), 1 on each fibula (upper third), 1 on each foot (below the lateral malleolus), and 1 at lumbar level (L5).

**Figure 3 figure3:**
[figure not shown]
Inertial measurement unit placements. 1: Thighs (side, upper third); 2: fibulas (upper third); 3: foot (below lateral malleolus); 4: Lumbar (L5 level).

##### Video Recording and Window Labeling

During each visit, and during trials designed to induce freezing episodes, patients will be recorded using 14 synchronized Miqus M3 cameras (Qualisys). These cameras will record at a resolution of 1824 × 1088 pixels with a frequency of 25 Hz. FoG episodes will be identified from the videos by 2 movement disorders specialists ([name]) independently using QTM 2020 software (Qualisys). The start of a freezing episode is defined as “the moment when the stepping foot does not leave the ground despite a clear intention to step,” and the end is defined as “the moment when the stepping foot begins or resumes an effective step” [32]. In cases where there is disagreement about the presence of a FoG episode, the specialists will discuss and reach a consensus. Following the methodology of Pardoel et al [32], the data timeline will be segmented into 2-second windows with a 0.4-second shift between windows (80% overlap). Windows will be labeled as “FoG window” when the entire window corresponds to a period of FoG. Windows not meeting this criterion, either during periods without FoG or during transitions between FoG episodes and non-FoG periods, will be labeled as “no-FoG window.” The relative duration of FoG will be assessed by calculating the ratio of FoG windows to the total number of windows. This ratio provides a measure of the freezing time while accounting for the window labeling method used. To ensure comparability with other studies and to mitigate the effect of varying labeling methods across research [32,38], we will also calculate the total number of FoG episodes and the cumulative freezing time based on onset and end events, categorized by task type, session, and patient. This approach will facilitate meaningful comparisons with existing literature on FoG detection methodologies.

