**Figure 1 figure1:**
[figure not shown]
Timeline of study. IMU: inertial measurement unit.

For organizational purposes, the first visit (inclusion visit) will occur during the “on” phase of levodopa medication, while the second visit (follow-up visit) will be during the “off” phase. During the “on” phase, patients will be assessed when oral treatment maximally improves dopa-sensitive PD symptoms (best “on” state, typically 1-2 hours after ingestion). This state will be determined based on patients’ subjective assessment, similar to their daily motor self-assessments (home diaries), which has been established as reliable in various studies [29-31]. Assessment during the “off” phase will occur after 12 hours without treatment, preferably in the morning before the first levodopa dose.

During each visit, participants will walk on a freezing-provoking path at a comfortable speed under 3 different clinical conditions (single task [ST], dual cognitive task [DCT], and dual motor task [DMT]). The Pardoel freezing-provoking path, known to induce FoG episodes [32], includes standing up, walking with a slalom (left and right turns), navigating a narrow passage with a 180° turn, and returning straight, with 2 designated stops—one chosen by the patient and another in front of a chair (Figure 2).

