### Data Management

All data are securely stored in a dedicated folder on a local server with restricted access limited to the research team. Patient’s clinical information (such as age, sex, laterality of symptoms, duration of PD, lateralization of symptom onset, daily dose of levodopa equivalent, FoGQ score, Hoehn and Yahr Scale rating, Schwab and England Scale assessment, and MDS-UPDRS III score) along with study results (videos and IMU data) are collected and controlled by the University Hospital of Rennes. A database containing video data is duplicated for each expert responsible for labeling FoG episodes. Time annotations will be exported as events in C3D files along with IMU data before the windowing process, contributing to a final database used for subsequent data analysis. This structured approach ensures the integrity and confidentiality of patient data while facilitating precise event annotation and thorough analysis of collected data.

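### No masking of the video readers to visit or medication state is described, although visit fixes the state and the labels feed the on/off comparisons

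*Protocol article*

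**What the plan says.** The reading procedure is in the protocol article under Video Recording and Window Labeling. There, "FoG episodes will be identified from the videos by 2 movement disorders specialists". The two readers work "independently using QTM 2020 software (Qualisys"), apply a stated start and end rule for an episode, and discuss any disagreement about whether an episode is present until they agree. The start rule requires a foot that stays on the ground although the patient clearly intends to step.

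Under Protocol, the medication state is tied to the visit for all patients: the first visit is in the on phase, and "the second visit (follow-up visit) will be during the" off phase.

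On the sensor side, IMU Measurements says of QTM 2020, which receives the IMU data: "The software manages recording at a sampling frequency of 148.15 Hz and synchronizes with cameras". Data Management says: "A database containing video data is duplicated for each expert responsible for labeling FoG episodes". It adds: "Time annotations will be exported as events in C3D files along with IMU data before the windowing process".

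The labels are then used in three places. Video Recording and Window Labeling derives episode counts and cumulative freezing time by task, session and patient. Model Training scores every window against the experts. Secondary Outcomes compares accuracy, sensitivity and specificity across task and medication state.

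**The concern.** The reference standard involves judgement, and the text places nothing between the reader and the medication state. Independence separates the two readers from each other. It does not separate either of them from the visit, and the consensus step brings them together with no masking mentioned. If both readers hold the same expectation about the off state, a second reader does not cancel it.

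Two sets of results are at stake. The freezing counts and freezing times by session are on/off results in themselves, because session and medication state coincide. The comparison of detector performance by state uses the same labels as the truth. Leave-one-subject-out validation would not expose a labelling tendency shared by all patients, because the same kind of label trains the model and scores the held-out patient.

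A second, lesser question is whether readers could see sensor traces while annotating. If they could, information from the test under study would reach its own reference standard.

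**Working it through.** The plan states no figure on this point, so there is none to reproduce. The check is a comparison of sections, followed by a short piece of algebra on what could be said about size.

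**1. Can a reader know the state?** Under Protocol, visit 1 is on and visit 2 is off for all patients. Knowing the visit is knowing the state. Neither Video Recording and Window Labeling nor Data Management says that files are coded, stripped of dates or shuffled. The article says neither that readers are masked nor that they are unmasked.

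**2. Is there room for judgement?** Partly. The end of an episode, and the foot staying on the ground, are observable. Whether the patient intended to step is inferred.

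**3. Do the labels reach an on/off result?** Yes, by two routes: counts and time by session, and performance by medication state. The primary outcome, accuracy per subject, also uses the labels but is not an on/off contrast.

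**4. Can readers see the IMU signal?** Three statements bear on this.
- Readers annotate in QTM 2020, which also holds the synchronised IMU data. This leaves a route open.
- Episodes are identified from the videos, and the readers' copies are described as video data. This points away from that route.
- Annotations are exported before windowing, so features and model output do not yet exist and cannot influence the labels. Raw traces are not ruled out by this.

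**5. Can direction or size be derived?** Hold the detector fixed, with the same sensitivity S in both states. Suppose knowledge of the state adds *a* extra FoG windows in the off state per existing FoG window, and the detector flags a share *f* of them.
- Off sensitivity = (S + f·a) / (1 + a).
- On minus off = S − (S + f·a)/(1 + a) = a(S − f)/(1 + a).

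The gap is positive if f < S, zero if f = S and negative if f > S. The documents give none of S, *a* or *f* for this detector, so neither the sign nor the size follows.

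The scoring rule adds a further limit. A window counts as FoG only if all 2 seconds are FoG, with a 0.4-second shift. An added episode shorter than 2 seconds yields no FoG window and cannot change sensitivity. One of at least 2 + 0.4 = 2.4 seconds always yields at least one. Short doubtful episodes would therefore mainly affect the episode counts and cumulative freezing time, which are taken from onset and end events.

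**The case against.** The strongest reply is that this is a condensed article. File coding, display layout and reading order may stand in a full protocol or a reading manual. That is fair, and a reader who infers that the readers **are** unmasked goes beyond the text, which supports only that no masking is described. The reply does not dispose of the point. The article fixes the readers, their independence, the software, the start and end rules and the consensus step, and a procedure followed as written there leaves the state open to view.

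A reader might also infer from the shared software that the labels are contaminated by the IMU signal. The documents do not support that. They describe reading from videos and from copied video data, completed before windowing. What stands is a route that is not explicitly closed.

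It is tempting to attach a number of percentage points to the on/off bias. Any such number would come from assumed inputs, and the algebra shows that even its sign depends on them. Nor do the documents say that the readers expect more freezing in the off state, or in which direction detector performance should differ.

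Finally, the harm need not be permanent. The videos are stored, so a masked re-reading would remain possible at the cost of the experts' time. And masking could only be partial, because motor signs may show on video. Both points stand. They limit the weight of the concern without removing the case for a nearly free safeguard.

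**Conclusion.** The point holds in a limited form. The article describes no masking of the two readers to visit or medication state, the fixed visit order makes the state easy to know, and part of the episode definition is a judgement. Knowledge of the state could bias the freezing counts and times by session and the performance comparison by medication state. The size and direction cannot be derived from the documents. The effect on the primary accuracy is less direct, because that outcome does not contrast the two states.

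Exposure to IMU traces is a matter to close in the text and not an established fault. The verdict assumes that no other document already provides masking. If one does, one sentence in the article settles the matter. This is a worthwhile, inexpensive improvement to the design; it does not show that the results will be wrong.

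**What to change.** In Video Recording and Window Labeling, state that:
- each reader receives video-only files with coded names that carry no visit, date or medication state;
- files are read in random order across visits and patients;
- IMU channels are removed or hidden in QTM during annotation;
- consensus is reached on the same masked files;
- annotations are locked before they are merged with the IMU data.

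Acknowledge in the same place that task type cannot be masked, because the tray and the spoken words are evident, and that motor signs may still hint at the state.

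The cost is a small script for renaming and shuffling, a QTM layout or export without the sensor channels, and a few lines of text. No extra reader, visit or patient is needed. The downside is that readers can no longer view one patient's session in sequence. Results reports 3 patients recruited by August 2024, with analysis to follow data collection, so the change was feasible at that date. If recordings have already been read without masking, the stored videos allow a masked re-reading of all of them or of a sample.

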### Data Management

All data are securely stored in a dedicated folder on a local server with restricted access limited to the research team. Patient’s clinical information (such as age, sex, laterality of symptoms, duration of PD, lateralization of symptom onset, daily dose of levodopa equivalent, FoGQ score, Hoehn and Yahr Scale rating, Schwab and England Scale assessment, and MDS-UPDRS III score) along with study results (videos and IMU data) are collected and controlled by the University Hospital of Rennes. A database containing video data is duplicated for each expert responsible for labeling FoG episodes. Time annotations will be exported as events in C3D files along with IMU data before the windowing process, contributing to a final database used for subsequent data analysis. This structured approach ensures the integrity and confidentiality of patient data while facilitating precise event annotation and thorough analysis of collected data.

### Data Analysis

#### Features Extractions

Each window of data will undergo normalization to achieve zero mean and unit variance. Our study distinguishes itself through an exhaustive exploration of features aimed at identifying FoG episodes. From each window, signal features will be extracted from both the time and frequency domains. A comprehensive array of features will be included, such as the number, duration, and length of acceleration or angular velocity reversals, kurtosis, and skewness [14]. Furthermore, we will incorporate metrics such as the magnitude of mean and SD of signals, as well as specific metrics related to smoothness such as spectral arc length measure [39] and the freezing ratio [40]. Nonlinear modeling features, such as sample entropy or Lyapunov exponent, which quantify gait regularity and complexity, will also be used [41]. Furthermore, measures of inter- and intralimb coordination will be integrated to highlight specific limb dynamics during FoG episodes. Feature selection will be conducted using Relief-F, chosen for its suitability in our application over methods such as minimum redundancy maximum relevance ranking [20]. This approach ensures that the selected features are highly relevant to distinguishing FoG episodes, thereby optimizing the accuracy and effectiveness of our analysis.

#### Model Training

The top-ranked features identified through Relief-F will be used in a decision tree (DT) model for classifying windows of data. The DT model will be tested using 5 and 10 decision splits and with various sets of top-ranked features ranging from 5 to 20. The performance of the DT model will be evaluated using metrics such as accuracy, sensitivity, specificity, PPV, and NPV. The model’s performance will be determined based on the classification of each window as true positive (TP), true negative (TN), false positive (FP), or false negative (FN), comparing the model’s classifications with the experts’ identification of FoG episodes on video recordings (Figure 4).

**Figure 4 figure4:**
[figure not shown]
Segmentation on true negatives (TNs), true positives (TPs), false negatives (FNs), and false positives (FPs) for each second according to the experts and the model.

The agreement between the model and experts regarding FoG or non-FoG periods will be assessed as follows:

TP: A FoG period correctly identified by both the experts and the modelTN: A non-FoG period correctly identified by both the experts and the modelFP: A FoG period incorrectly identified by the model but not by the expertsFN: A FoG period incorrectly identified by the experts but not by the model

Performance scores will be calculated using the following equations:

[figure not shown]

#### Model Validation

The model validation will use the leave-one-subject-out (LOSO) cross-validation technique to assess its performance across participants and accommodate the considerable variability between participants. While some studies [20,42] advocate for the leave-one-freezer-out (LOFO) cross-validation technique to avoid overrepresentation of patients without FoG in training and validation sets, our study focuses on participants who have experienced at least 1 episode of FoG during their initial visit. Consequently, each patient will have FoG episodes, making the LOSO approach more suitable for our validation process.

### Statistical Analysis

Clinical data of the participants will be presented as means (SD) or medians with IQRs for continuous data, depending on their distribution. Categorical data will be reported as counts (with percentages within parentheses).

#### Primary Outcome

The main objective of our study is to identify the most relevant features and locations of wearable sensors for detecting FoG episodes. The Relief-F technique will rank features extracted from data collected by all sensor segments. The top-ranked features across all subjects will indicate the most critical sensors for detecting FoG episodes, and these features will be used in model training and validation. The LOSO method will be used for validation, and accuracy will be computed for each subject. Furthermore, Relief-F analysis will be conducted individually for each subject to potentially reveal redundancy in the top-ranked features across subjects. Feature extraction, selection, model training, and validation will be implemented using Python 3.0 (PythonLabs) scripts.

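### Relief-F ranks features on 80%-overlapping windows with no stated limit on eligible neighbours, so the sensor ranking can favour slowly varying or trial-specific features unrelated to FoG

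*Protocol article*

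**What the plan says.** The IMU Measurements section fixes the unit of analysis: "IMU data will also undergo windowing with a 2-second window length and a 0.4-second shift". The Video Recording and Window Labeling section repeats these values and gives the overlap as 80%. It sets the label rule: "Windows will be labeled as “FoG window” when the entire window corresponds to a period of FoG". Every other window, including those that straddle the edge of an episode, counts as no-FoG.

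Under Features Extractions, "From each window, signal features will be extracted from both the time and frequency domains", and "Feature selection will be conducted using Relief-F, chosen for its suitability in our application". That section goes on to assert that the approach guarantees features strongly relevant to telling FoG apart.

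Under Primary Outcome, which describes finding the relevant features and sensor locations as the main objective, "The Relief-F technique will rank features extracted from data collected by all sensor segments". The pooled ranking is to show which sensors are critical, and its top features feed the decision tree. Relief-F is also to be run within each subject. LOSO is named for validation. The article gives neither k nor any limit on which windows may serve as neighbours.

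**The concern.** Relief-F weights a feature by its average difference to the nearest windows of the other class (misses) minus its average difference to the nearest windows of the same class (hits). When windows overlap heavily, a window's closest hits are often its own neighbours in time, cut partly from the same signal. Misses overlap it less often, because a change of class usually means a different stretch of recording. A feature that drifts slowly, or mainly marks the trial, then has small hit differences and larger miss differences. It gains weight with no link to FoG.

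At stake is the answer to the study's main question. Sensors could be named as critical because their signals are stable within a trial. LOSO keeps patients apart when the classifier is scored, but it does not restrict neighbours in the ranking. The per-subject runs are no check, since all their neighbours come from the same patient and the overlap remains.

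**Working it through.** **Inputs from the protocol article.** Window 2 s and shift 0.4 s (IMU Measurements; Video Recording and Window Labeling); FoG label only if the whole window is FoG; 18 patients; 5 to 20 top features kept (Model Training).

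**1. The plan's own figure.** Overlap = 1 − shift/length = 1 − 0.4/2 = 0.80. The stated 80% is reproduced.

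**2. How many windows can overlap.** Windows 1, 2, 3 and 4 shifts away share 80%, 60%, 40% and 20% of their data. The fifth starts 5 × 0.4 = 2 s later and shares none. The maximum is 2 × 4 = 8.

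**3. Ceiling on the overlapping share of k hits.** This is 8/k: 80% at k = 10, 50% at k = 16, 40% at k = 20, 16% at k = 50, 8% at k = 100. A majority is impossible from k = 16 upward.

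**4. Episode length.** An episode of D seconds yields floor((D − 2)/0.4) + 1 FoG windows: 1 at 2 s and 6 at 4 s. A FoG window can have all 8 overlapping hits within its episode only if the episode holds 9 FoG windows, so D ≥ 2 + 8 × 0.4 = 5.2 s.

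**5. Main simulation.** Relief-F with Manhattan distance on range-scaled features, using the article's windows and label rule. Assumptions not in the documents: k = 10; 8 patients × 10 trials × 40 s; episodes of 3–10 s; 65 features, of which 5 shift with FoG by 1 SD, 40 are fast noise and 20 are slow noise (correlation time 5 s). One seed per scenario.

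In the base case, 61% of the 10 nearest hits of FoG windows and 66% of those of no-FoG windows overlapped the index window. For misses the shares were 13% and 4%.

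Mean weights (× 1000):

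| Setting | Slow, unrelated | True FoG | Slow features above the weakest true one |
|---|---|---|---|
| Base (k = 10, 1 SD) | 52.7 | 38.8 | 20 of 20 |
| Base, neighbours from other trials only | 2.8 | 22.8 | 0 of 20 |
| 18 patients | 46.7 | 35.4 | 20 of 20 |
| 18 patients, other trials only | 2.1 | 22.2 | 0 of 20 |
| k = 20 | 32.6 | 32.3 | 18 of 20 |
| k = 50 | 16.3 | 28.2 | 0 of 20 |
| k = 100 | 10.6 | 27.5 | 0 of 20 |
| 1.5 SD | 55.6 | 60.1 | 12 of 20 |
| 2 SD | 53.0 | 86.7 | order not upset |
| Unrelated as fast as FoG features | 20.0 | 40.7 | 0 of 20 |

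In the base case all 20 top places went to slow unrelated features. With neighbours from other trials only, all 5 true features were in the top 20.

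**6. A milder mask.** Excluding only overlapping windows left 6.8 against 21.9 in the base case. When trials differed from each other it left 16.2 against 17.6, so it is not enough for trial-specific features.

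**7. Separately built simulations.** One used 18 patients, about 12% FoG windows, 10 relevant and 30 irrelevant features, k = 10 and six repetitions. With 15 of the irrelevant features slow, irrelevant features took 20–100% of the top 10 at 1 SD, 2–30% at 1.5 SD and 0–3% at 2 SD (the last for patient-level variance shares of 0 and 30% only). With neighbours from other patients these became 5–8%, 0% and 0%. If all irrelevant features varied fast there was no distortion. Another, at k = 10 and 1 SD, had 65% of hits and 11% of misses overlapping, and slow unrelated features in 9 of the top 10 places. Excluding same-trial or same-patient neighbours restored all 5 true features. There the true features kept their rank at 2 SD, or from k = 30.

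**The case against.** **Silence is not a statement.** A reader might infer that the plan treats windows as independent. The article does not say so, and k, the distance and neighbour rules are details that a full protocol may hold. That stands. What remains is what the article does commit to: an unqualified Relief-F ranking on heavily overlapping windows, used to name sensors, with an assurance of relevance that the combination does not give.

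**Most hits need not be near-copies.** This stronger reading is tempting but unsupported. It depends on k, fails from k = 16, and 4 of the 8 overlapping windows share only 20% or 40% of their data. With 12 features the overlapping share fell to 31–34%.

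**Misses overlap too.** Transition windows labelled no-FoG lie beside FoG windows and act as overlapping misses. With 2–4 s episodes, 41% of the misses of FoG windows overlapped against 33% of hits. This offsets part of the effect near episode edges, yet slow noise still led in that run (55.8 against 39.4).

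**Real features may be stronger than 1 SD.** The Introduction cites sensitivity 84.3% and specificity 78.4% for the freezing index alone. Under an equal-variance normal model that is about 1.0 + 0.8 = 1.8 SD, where distortion is small. This is a rough conversion for one feature; weaker ones remain exposed.

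**Normalisation.** Scaling each window to zero mean and unit variance, read literally, removes level and amplitude, two obvious carriers of trial or patient identity. The simulations did not model it. Spectral or entropy features could still vary slowly or mark a trial.

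**LOSO would show up poor features.** It would tend to, through low accuracy, and a tree need not split on a useless feature. But LOSO scores the classifier; it does not test whether the sensors named as critical are the right ones.

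**Conclusion.** The concern holds in a limited form. As described, the ranking can favour slowly varying or trial-specific features over features that change with FoG, and the assurance under Features Extractions is not justified.

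The size cannot be fixed from the documents. With k about 10 and FoG effects near 1 SD, simulation shows serious distortion. With effects near 2 SD, k of 50 or more, or unrelated features that vary as fast as the FoG features, the true features keep their rank. The simulations rest on assumed signal properties and few repetitions, so they give direction and range and do not predict this trial's results.

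A reader might also infer that the selected features will perform worse in new patients. No decision tree or LOSO accuracy was simulated, so that is not shown. The harm established as possible is to the feature and sensor ranking. Because that ranking answers what the Primary Outcome section calls the main objective, and the remedy is cheap, it should be corrected before analysis starts.

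**What to change.** Under Primary Outcome, state k, and state that in both the pooled and the per-subject Relief-F rankings the nearest hits and misses of a window are searched only among windows from other trials. For the pooled ranking, restricting the search to other patients is an acceptable alternative that matches the LOSO target. Soften the assurance under Features Extractions accordingly. Windows, labels, features and Relief-F itself stay as planned.

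The cost is a mask on the neighbour search and one sentence; no new data are needed. According to the Results section, analysis begins only once all data are gathered, so the rule can still be set in advance if that has not happened.

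There are two small downsides. Fewer neighbours are eligible: a patient whose FoG windows all fall in one trial has no eligible hit for them in the per-subject run, and the plan should say how such a patient is reported. If the other-patients rule is chosen, features that are informative only relative to a patient's own level get less credit in the pooled ranking, though the per-subject ranking still shows them.
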